#### Randomisation method

Knowing that 375 participants were needed, we were advised to undertake block randomisation stratified by centre, sex and age group (female: <75 vs ≥75 years, male: <80 vs ≥80 years). Randomisation uses the web application Research Electronic Data Capture (REDCap https://www.project-redcap.org/).

### Statistical analysis

Daily screening logs will be kept determining: (i) the total number of days (n) where patients were approached in each centre and (ii) the daily totals of PHOENIX invitation packs distributed. This log will also record if a numbered pack was not given out on a day (eg, if the patient did not arrive for scanning, or the receptionists omitted to give out the pack). The total number of consented individuals (x) as well as the number of consented individuals per day (total x/n overall, and per centre) will be calculated. The number of consented but subsequently excluded individuals (y) will be kept (eg, for subsequently discovered metalwork in the scan, technical issues with scan). The number of randomised participants will be calculated (z=x−y), and the rate of randomisation (z/n overall, and per centre). These data will be captured from screening logs and entered manually onto a database. The REDCap database will be used to record details of all consenting patients (z). The database will be locked on completion of data entry and when missing data or any discrepancies are resolved. The data will be exported for statistical analysis to the study statisticians with assistance from the chief investigator.

#### Predefined statistical analysis plan

Response rates will be calculated as the proportion of participants invited who (a) consent to take part, (b) meet eligibility criteria and (c) are randomised, with 95% CIs to assess the extent to which the realised response deviates from the expected as detailed in the power calculations above. Cumulative participant accrual over time will be plotted overall and by recruitment centre to assess any major differences in accrual and assess progress towards target. Logistic regression will be used to compare randomised groups with respect to the 12-month outcomes of treatment rates and participant retention. Baseline stratification covariates (ie, centre, sex and age) will be adjusted for in the models. Analyses will be on an intention-to-treat basis.

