**Methods and analysis:**

A multicentre, randomised, pragmatic feasibility study. From the general CT-attending population, women aged ≥65 years and men aged ≥75 years attending for CT scans are invited to participate, via a novel consent form incorporating Fracture Risk Assessment (FRAX) questions. Those at increased 10-year risk (within the amber or red zones of the UK FRAX graphical outputs for further action) are block randomised (1:1:1) to (1) PHOENIX intervention, (2) active control or (3) usual care. The PHOENIX intervention comprises (i) retrieving the CT scans using the NHS Image Exchange Portal, (ii) Mindways QCT Pro software analysis of CT hip and spine none density with CT vertebral fracture assessment, (iii) sending the participants’ general practitioner (GP) a clinical report including diagnosis, necessary investigations and recommended treatment. Baseline CT scans from groups 2 and 3 are assessed with the PHOENIX intervention only at study end. Assuming 25% attrition, the study is powered to find a predicted superior osteoporosis treatment rate with PHOENIX (20%) vs 16% among patients whose GPs were sent the FRAX questionnaire only (active control) and 5% in the usual care group. Five hospitals are participating to determine feasibility. The co-primary feasibility outcome measures are (a) ability to randomise 375 patients within 10 months and (b) retention of 75% of survivors, completing their 1-year bone health outcome questionnaire. Secondary 1-year outcomes include osteoporosis/vertebral fracture identification rates and osteoporosis treatment rates. Stakeholder acceptability and economic aspects are evaluated.

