#### Power for treatment proportions

Assuming that osteoporosis treatment percentages at 1-year follow-up in the usual care versus active control FRAX-GP versus PHOENIX intervention would be 4.5% vs 15.5% vs 20.3%, respectively (ie, as observed in SCOOP trial vs with expected improvement in PHOENIX), a total of 375 participants recruited and randomised in the ratio 1:1:1 will have 96% power (figure 4G) to detect linear trend in treatment proportions based on a two-sided test of binomial proportions at 5% statistical significance level. The same sample size will have 93% power for a secondary two-degree of freedom test of between-group contrasts in comparison with usual care. When allowing for up to 25% attrition due to non-differential dropout or incompleteness of outcomes, the remaining sample size of 280 participants will have >84% power to detect the same magnitude of differences (figure 4G).

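### The protocol presents PHOENIX's gain in treatment rate over the FRAX-to-GP arm as powered and detectable, but its power figures belong to a linear trend and a 2-df test; power for that contrast is about 13–17%

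*Protocol article*

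**What the plan says.** Four places in the Protocol article bear on the 12-month treatment comparison.

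- **Abstract, Methods and analysis.** Allowing for 25% attrition, "the study is powered to find a predicted superior osteoporosis treatment rate with PHOENIX (20%) vs 16% among patients" in the FRAX-to-GP arm; the sentence goes on to give 5% for usual care.
- **Sample size calculations, study power, randomisation method.** The expected 4.8-point gain from PHOENIX is called the minimum detectable difference. Measured against 15.5% in active control, it is said to be clinically significant.
- **Power for treatment proportions.** The 12-month rates for usual care, active control and PHOENIX "would be 4.5% vs 15.5% vs 20.3%, respectively". On these, "a total of 375 participants recruited and randomised in the ratio 1:1:1 will have 96% power" "to detect linear trend in treatment proportions based on a two-sided test of binomial proportions at 5% statistical significance level". Then: "The same sample size will have 93% power for a secondary two-degree of freedom test of between-group contrasts in comparison with usual care". After attrition, "the remaining sample size of 280 participants will have >84% power to detect the same magnitude of differences".
- **Predefined statistical analysis plan.** "Logistic regression will be used to compare randomised groups with respect to the 12-month outcomes of treatment rates and participant retention", adjusted for centre, sex and age, by intention to treat.

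Treatment initiation is a secondary outcome (Box 2). The arm-level percentages are to inform power calculations for a future trial (opening paragraph of Methods and analysis).

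**The concern.** The first two places tell the reader that the study can detect PHOENIX's advantage over sending the FRAX answers to the GP. The third quotes power for two tests, and neither is that comparison. One is a trend across three ordered arms. The other is a 2-df test against usual care. Both can be highly significant because the two active arms differ from usual care, whatever the difference between those two arms.

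This matters because the middle arm has its own purpose: to see whether GPs act on a populated FRAX questionnaire alone. Whether CT densitometry adds to that is the question on which the extra work of the PHOENIX intervention turns. A reader who takes the power statement at face value could read a significant trend as support for PHOENIX over FRAX-to-GP, or a non-significant direct contrast as evidence that PHOENIX adds nothing. Neither reading would be warranted, and either could carry over into planning the definitive trial.

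**Working it through.** **Inputs (Power for treatment proportions).** Rates 4.5% / 15.5% / 20.3%; 375 randomised 1:1:1, so n = 125 per arm; two-sided 5%; 280 left after attrition, about 93 per arm. Equally spaced trend scores are an assumption, since the article gives none; they reproduce its figure.

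**1. Reproduce the plan's figures.**

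*Trend.* With scores −1, 0, 1 and equal arms, the statistic is (number treated on PHOENIX) − (number treated on usual care). The active-control count enters only through the pooled rate p̄ in the null variance.
- p̄ = (0.045 + 0.155 + 0.203)/3 = 0.1343
- Expected value = 125 × (0.203 − 0.045) = 19.75
- Null SD = √(2 × 125 × 0.1343 × 0.8657) = 5.39
- SD under the alternative = √(125 × (0.045 × 0.955 + 0.203 × 0.797)) = 5.06
- Power = Φ((19.75 − 1.96 × 5.39)/5.06) = Φ(1.81) = 96.5%. The plan states 96%.

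*2-df test.* Non-centrality = n Σ(pᵢ − p̄)² / (p̄(1 − p̄)) = 14.1, giving 93.0%. The plan states 93%.

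*At 280 in total.* Trend 90.1%, 2-df 83.6%. The plan states above 84%, which the trend meets and the 2-df test meets to rounding.

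So the stated powers are right for the tests they name.

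**2. Power for each pairwise contrast.** Power = Φ((d − 1.96 × SE₀)/SE₁), with SE₀ from the pooled rate and SE₁ from the separate rates.

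For PHOENIX v active control, d = 0.203 − 0.155 = 0.048 and the pooled rate is 0.179.
- 125 per arm: SE₀ = √(2 × 0.179 × 0.821/125) = 0.0485, SE₁ = 0.0484; Φ((0.048 − 1.96 × 0.0485)/0.0484) = Φ(−0.97) = 16.6%
- 93 per arm: SE₀ = 0.0562, SE₁ = 0.0561; Φ(−1.11) = 13.4%

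| Contrast | 125 per arm | 93 per arm |
|---|---|---|
| PHOENIX v usual care | 97.0% | 91.1% |
| Active control v usual care | 83.0% | 70.9% |
| PHOENIX v active control | 16.6% | 13.4% |

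Simulation (200,000 trials per scenario, unadjusted tests) gives 98% and 93% for PHOENIX v usual care, and 16% and 13% for PHOENIX v active control.

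The usual sample size formula on the same basis needs 1001 per arm for 80% power at 15.5% v 20.3%. That is 3003 in three arms, or 3003/0.75 = 4004 with 25% attrition. With the Abstract's rounded 16% v 20% it is 1447 per arm.

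**3. What the powered tests do when PHOENIX adds nothing.** With rates 4.5 / 15.5 / 15.5% in simulation:
- the trend is significant in 80% of trials at 125 per arm and 66% at 93;
- the 2-df test is significant in about 86% and 73%;
- PHOENIX v active control is significant (two-sided) in about 5%, as it should be.

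**4. The design scenario as one data set.** The expected counts at 125 per arm are 6, 19 and 25 treated. Logistic regression without covariates gives trend p = 0.0006 and PHOENIX v usual care p = 0.0007. PHOENIX v active control has odds ratio 1.39 (95% CI 0.72 to 2.69), p = 0.32. In simulation at the design rates, the trend is significant while PHOENIX does not significantly beat active control in 81% of trials.

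**The case against.** **This is a short article, and the outcome is secondary in a feasibility study.** Coding of arm, order of contrasts and control of multiplicity are commonly left to a full analysis plan, which is not shown. This stands. A reader might infer that the plan has no deciding test and an inflated familywise error. The document does not support that as a finding: the power section ranks the trend first and calls the 2-df test secondary, and strict error control for a secondary feasibility outcome is a matter of preference.

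**Logistic regression does not conflict with the power section.** Arm entered as an ordered score gives the trend; arm entered as a factor gives the 2-df test and the contrasts. This also stands. A reader might infer that the sizing test and the analysis would give conflicting answers. Under the plan's own rates, the trend and 2-df tests disagree in only 3% of simulated trials (7% at 93 per arm). The serious divergence is with PHOENIX v active control.

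**The Abstract sentence describes a three-arm pattern.** It does name usual care as well. But it gives PHOENIX v active control first, as a superiority that the study is powered to find, and the sample size section separately calls that 4.8-point gain detectable. The three-arm reading does not rescue those statements.

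**Future planning uses arm-level percentages, and nowhere is a significant trend said to be reportable as superiority over active control.** Correct. The risk is one of reading, created by the power description, and not a declared intention.

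**Conclusion.** The point holds as a misdescription of power. The 96% and 93% figures are correct for the trend and the 2-df test. They do not extend to PHOENIX v active control, for which power is about 16–17% at 125 per arm and 13–14% at 93 per arm. The latter is the setting of the Abstract's claim, which allows for 25% attrition. A significant trend or 2-df test cannot establish that PHOENIX improves on sending the FRAX answers: the trend is significant in about 80% of trials (66% after attrition) when the two arms have the same rate.

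These figures assume the plan's own rates, equal arms, equally spaced scores and unadjusted two-sided 5% tests. Adjusting for the stratification covariates is not expected to close so large a gap. The conclusions on recruitment and retention, which are the co-primary outcomes, are unaffected.

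**What to change.** 1. **Abstract, sample size section and Power for treatment proportions.** State that the power applies to the trend and to comparison with usual care. For PHOENIX v usual care, quote about 97–98% at 125 per arm and 91–93% at 93 per arm. Remove the statements that PHOENIX v active control is powered and that 4.8 points is detectable. The 4.8 points may remain as the difference regarded as clinically significant.
2. **Predefined statistical analysis plan.** Name PHOENIX v usual care, from the adjusted logistic model, as the main treatment contrast. Report PHOENIX v active control from the same model as an estimate with a 95% CI, labelled not powered. State that a significant trend or 2-df test is not evidence of superiority over active control.

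The cost is wording only, with no extra patients or data. The downside is a less favourable description of power: the study can no longer be presented as able to show superiority over FRAX-to-GP.

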### Qualitative analysis and stakeholder acceptability research

Both the baseline and 1-year follow-up questionnaires being sent to all patients include space for participants to feedback their experience of the study. First explaining how this will help, this section includes example open questions such as *“Do you have any comments on being offered a bone health check at the same time as your CT scan? Or on taking part in this research study?/how you were asked to join?/your decision to take part?’*. Semi-structured interviews will be used with a smaller subsample of study participants (n=20) to allow for more in-depth exploration of issues that participants may raise in written feedback or during interview. Recordings will be transcribed by an academic transcription service following a confidentiality contract and anonymised by a member of the research team (JF) changing names of people and places and any identifiable details. Key research questions for the PHOENIX process evaluation are: (i) what are the implementation facilitators and barriers for the PHOENIX intervention? (ii) how acceptable to the intended patient group is the process of PHOENIX screening? (iii) how do implementation and acceptability issues affect uptake of the CT bone health screening and any subsequent GP investigation and recommended bone protective treatment? A combination of interviews and focus groups with those staff groups who will be key to the effective delivery of PHOENIX screening will also be undertaken, both in hospital and primary care, in order to understand their different perspectives. These staff groups are research nurses, receptionists and radiographers in CT departments and GPs. Analyses will be descriptive. The software programme NVivo V.12 (QSR) will be used to manage and index the qualitative data (anonymised transcripts of audio-recordings from interviews and focus groups) before charting, mapping and interpretation taking a framework approach.^10^ Ritchie and Spencer thematic analysis is an approach suitable for qualitative research in which data collection is relatively focused on key questions,^11 12^ hence it is applicable to PHOENIX.

### Patient and public involvement

At the ‘idea’ stage of the research, our small team presented our idea at the large workshop *“Find your voice; Demystifying research and public involvement in research”* at Cambridge Professional Development Centre Trumpington in May 2015. This was run by [name] Patient and Public Involvement and Engagement (PPIE) lead for the Eastern region NIHR Research Design Service in partnership with the Norfolk and Suffolk PPIRes team (PPI in research). This connected us with patients and public representatives, many of whom had relevant musculoskeletal disorders and/or past experience in an orthopaedic service. We collated the opinions and suggestions on our proposed project from every participant in the workshop in writing, individually and from small group discussions to help develop our research question and outcome measures, so that they were informed by patients’ priorities, experiences and preferences. Three individuals, [name], [name] and [name] volunteered to join our trial group as PPI representatives; they were specifically involved in patient documentation design (particularly the PHOENIX pack, informed consent form which facilitated consent without having a researcher present) and contributed to suggestions for increasing patient recruitment and follow-up. JF facilitated group sessions and individual structured interviews to assess the burden of the PHOENIX intervention on patients themselves, as well as a qualitative assessment of the process from a user perspective. The results of the research will be disseminated to surviving participants after generating patient-friendly materials in collaboration with our PPIE representatives.

### Economic analysis

Completion rates on the quality-of-life measure (EQ-5D-5L) and resource use items included within the postal survey will inform whether an economic evaluation is feasible using these data collection approaches in the definitive trial. Patterns of response and non-response will be explored to see if they suggest ways the postal survey can be refined to improve data completeness.

## Ethics and dissemination

Approved by committee (National Research Ethics Service) East of England (EE) as REF/19/EE/0176. Dissemination will be through the Royal Osteoporosis Society Bone Academy (to patients and public) as well as to clinician peers via national and international bone/rheumatology scientific and clinical meetings.

## Data Availability

Data are available on reasonable request. Researchers involved in the trial will have access to the full dataset. Applications for access to the final trial dataset will be through the Trial Management Group (TMG). All members of the TMG will have full access to the dataset, and a controlled access model (openly available to all applicants) will be followed as set out in the MRC and NIHR guidance (https://www.methodologyhubs.mrc.ac.uk/files/7114/3682/3831/Datasharingguidance2015.pdf).
